### Randomization

Schools within each country will be randomly allocated to control or intervention arm using Microsoft excel (Microsoft 365) RAND function. Allocation will remain for the duration of the project.

### Blinding

Blinding will not be possible in this cRCT. Due to the nature of the intervention, participants will be aware of whether they are in the intervention or control arm.

### Intervention

The “Magic Glasses” education package will be comprised of two animated cartoon packages developed specifically for the Lower Mekong setting: (1) MGO, an educational cartoon addressing OV infection, including transmission, symptoms, treatment, and prevention, and (2) MGLM, an educational cartoon addressing STH infection, including transmission, symptoms, treatment, and prevention. Each package includes an educational cartoon, an accompanying comic pamphlet with key messages and images from the cartoon, and engaging reinforcement activities for students (drawing competition and essay competition).

#### Cartoon Production

The MGO and MGLM interventions were adapted from previous Magic Glasses interventions [30,31], informed by literature reviews on risk factors and KAP regarding STH and OV in LMB. In line with previous “Magic Glasses” cartoons, the health messages of the cartoon were informed by developmental psychology theories including the Theory of Planned Behavior [40] and Social Cognitive Theory [41] to promote engagement and effectiveness with schoolchildren. In order to ensure that the cartoon style and backgrounds are relevant to SEA audiences, the cartoons were produced by 2D animation company, a Thai animation company based in Khon Kaen. Once the Thai versions of MGO and MGLM were finalized, Cambodian and Lao versions of each cartoon were adapted to include culturally appropriate attire and local languages (see Figure 1). The dialogues for each country’s cartoons were then recorded by voice actors in Thai, Khmer, and Lao. In total, 6 cartoons were developed.

**Figure 1 figure1:**
[figure not shown]
Cambodia, Lao, and Thai versions (left to right) of the Doctor character in the “Magic Glasses Opisthorchiasis” and “Magic Glasses Lower Mekong” educational cartoons.

#### Comic Pamphlet

A comic pamphlet was developed for OV and STH summarizing the key health messages for each cartoon. The images included in the OV and STH comic pamphlet were taken from the health message summary at the end of the MGO and MGLM cartoon, respectively.

### Study Procedures

Study commencement will be staggered across Thailand, Cambodia, and Lao PDR, based on the school periods in each country. Prior to study commencement and intervention delivery, all study materials will be translated into the local language by the local research team in each country. For anticipated study dates in each country, see Multimedia Appendix 1.

#### Baseline KAP Assessment

Prior to intervention delivery, all consenting participants in Grades 3-6 in control and intervention schools will complete 2 questionnaires on KAP surrounding OV and STH. The first questionnaire will include questions on demographic information and students’ knowledge of OV, including general knowledge, transmission, symptoms, and treatment; attitudes and health education, and behavior. The second questionnaire will follow the same format to assess students’ knowledge of STH. The STH KAP questionnaire is a validated questionnaire used in previous “Magic Glasses” projects [30,31]. The OV KAP questionnaire was adapted from the STH KAP and reviewed by disease experts on the project prior to finalization (see Multimedia Appendices 2 and 3 for questionnaires). Paper questionnaires will be administered in classrooms by research staff and completed by students individually. To minimize confusion between OV and STH, baseline questionnaires for the respective infections will be administered on separate days.

#### “Magic Glasses Opisthorchiasis” Delivery and Acceptability Assessment

In intervention schools, the OV-baseline KAP assessment and OV intervention will be administered on the same day. Once OV-baseline KAP assessment has been completed, the MGO intervention package will be administered. MGO will be presented to schoolchildren and teachers in their classroom twice. Once the cartoon has been shown, schoolchildren will receive a comic pamphlet with the key messages of the cartoon. A classroom discussion will then be held to go over the messages and clarify any confusion among the students. Following the classroom discussion, an acceptability questionnaire will be administered to assess students’ initial acceptability of the cartoon. As with the KAP assessment, paper questionnaires will be administered in classrooms by research staff and completed by students individually. The acceptability questionnaire will contain multiple-choice and open-ended questions (see Multimedia Appendices 4 and 5). The questionnaire was adapted from the TFA [38] to include age-appropriate language for the schoolchildren, and specific questions on OV. Once the acceptability assessment is completed, the homework drawing competition will be explained: students will be asked to draw warning signs of OV infection, using the messages from the cartoon and comic pamphlet as a guide.

A reinforcement session will be held 6-8 weeks after the first presentation of MGO. The cartoon will be replayed twice to the student cohort, followed by a classroom discussion and explanation of the homework essay competition. Students will be asked to identify people who are at risk of liver fluke infection and write down why they are at risk, and how they can avoid liver flukes.

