#### “Magic Glasses Lower Mekong” and Acceptability Assessment

In intervention schools, delivery of the MGLM intervention package will take place on the same day as the STH KAP questionnaire, once baseline data collection is complete. The MGLM package will follow the same delivery procedures used for the MGO intervention package.

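### In intervention schools, the second disease's baseline KAP score is taken after the first cartoon package has been delivered

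*Protocol article*

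**What the plan says.** Four statements in the protocol article's Study Procedures fix the schedule.

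- The Baseline KAP Assessment section, on timing in both arms: "Prior to intervention delivery, all consenting participants in Grades 3-6 in control and intervention schools will complete 2 questionnaires on KAP surrounding OV and STH". OV is described first; for STH, "The second questionnaire will follow the same format to assess students’ knowledge of STH".
- The same section, on spacing: "baseline questionnaires for the respective infections will be administered on separate days". The interval is not given.
- The section on delivering Magic Glasses Opisthorchiasis, on when the package is given: "In intervention schools, the OV-baseline KAP assessment and OV intervention will be administered on the same day". The only condition set for starting it is the OV questionnaire: "Once OV-baseline KAP assessment has been completed, the MGO intervention package will be administered". The package is the cartoon shown twice, a pamphlet, a class discussion and, after the acceptability questionnaire, a drawing task for homework.
- The section on Magic Glasses Lower Mekong, on when the STH package is given: "delivery of the MGLM intervention package will take place on the same day as the STH KAP questionnaire, once baseline data collection is complete".

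Under Data Analysis (Quantitative), the OV and STH KAP scores are the primary outcome and are analysed separately. Changes in score go into linear regression, and GEE models compare the arms at baseline and follow-up. The Power section targets a 5-point difference in knowledge with 227 pupils, rounded to 228 in each country.

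**The concern.** A baseline should be measured before any part of the randomised intervention. Here one of the two primary outcomes has a baseline that is pre-exposure in control schools and post-exposure in intervention schools.

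Carry-over between the diseases is plausible. Both packages cover transmission, symptoms, treatment and prevention of a worm infection, and the OV questionnaire was adapted from the STH one. The protocol separates the questionnaires because it expects pupils to confuse the two diseases, so it already recognises interference between them.

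If the first package moves the second baseline, an analysis that subtracts or adjusts for that baseline removes part of the intervention's effect, or adds to it. An arm difference in that baseline could then reflect chance imbalance or carry-over, and the two could not be told apart.

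**Working it through.** **Scheduling.** Let A be the day of the OV baseline and MGO, and B the day of the STH baseline and MGLM, with A and B different days.

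- A before B: the STH baseline follows MGO.
- B before A: the OV baseline follows MGLM.

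No order puts both baselines before both packages. The unseen dates in Multimedia Appendix 1 cannot change this while all three rules hold. The condition that baseline data collection be complete applies to MGLM. MGO waits only for the OV questionnaire. In the order in which the article lists the questionnaires, STH is the affected outcome.

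**Bias.** Let the true effect at follow-up be d, and let the first package shift the second baseline by c points in the intervention arm only.

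- Change score or difference-in-differences: expected estimate = d − c.
- Baseline-adjusted regression with within-arm slope r: expected estimate ≈ d − r·c.
- Follow-up scores only: expected estimate = d.

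**Reproducing the stated sample size.** The article gives 80% power, a 5-point difference, design effect 2 and 10% attrition, but no SD or alpha. Assume a two-sided 5% test of two means with SD 9:

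- n per arm = 2 × (1.96 + 0.84)² × 9² / 5² ≈ 51
- 51 × 2 arms × design effect 2 = 204
- 204 / 0.9 = 227, as stated

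SD 9 is thus back-solved from the 227, not a documented figure.

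**Illustration, per country.** Effective n per arm = 228 × 0.9 / 2 arms / 2 = 51.3. SE = 9 × √(2/51.3) = 1.78. Power = Φ(estimate/SE − 1.96). True effect d = 5; r = 0.5 assumed.

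| c | Change-score estimate | Power | Adjusted estimate | Power |
|---|---|---|---|---|
| 0 | 5.0 | 80% | 5.0 | 80% |
| 1 | 4.0 | 61% | 4.5 | 72% |
| 2 | 3.0 | 39% | 4.0 | 61% |
| 3 | 2.0 | 20% | 3.5 | 50% |

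The SE is held at 1.78 throughout, so the adjusted column takes no credit for the precision that adjustment usually brings.

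**Pooled over three countries.** Effective n per arm = 684 × 0.9 / 2 / 2 = 153.9. SE = 9 × √(2/153.9) = 1.03. At an estimate of 3, power = Φ(2.92 − 1.96) ≈ 83%.

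**Opposite sign.** With c = −2 the change-score estimate is 5 + 2 = 7 and the adjusted estimate about 5 + 1 = 6, so the effect is overstated.

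**The case against.** The strongest reply is that the trial's stated hypothesis concerns KAP scores at follow-up. A between-arm contrast at that time does not use the exposed baseline, and the GEE model can supply it. This stands. The bias is confined to change-score, difference-in-differences and baseline-adjusted estimates, and the article does not say which estimate is primary. But it does plan an analysis of changes, so the exposed baseline will be used.

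Four stronger readings are tempting, and the documents do not support them.

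- **A bias towards no effect.** That requires positive carry-over. Similar questionnaires and topics point that way, but the transmission routes differ (soil versus raw or undercooked fish), and the protocol's own worry is confusion between the diseases. Confused pupils could score lower at the second baseline, which would inflate the effect.
- **A trial-wide fall in power to 39%.** That figure is per country, applies to change scores only, and rests on an assumed c of 2 and a back-solved SD. The sample size was also set for knowledge, whereas the primary outcome is the KAP score.
- **An outright contradiction with the statement that both questionnaires come before delivery.** That statement can be read as each questionnaire preceding its own package. This removes the conflict but leaves the second baseline post-exposure.
- **Baselines in Lao PDR and Thailand already affected.** The article says only that the trial is in progress there. It does not give each country's visit order or say how far baseline collection has gone.

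**Conclusion.** The scheduling point holds without assumption: under the rules as written, one disease's baseline in intervention schools must follow the other disease's package. The bias formulas follow directly: minus c for change scores, about minus r·c with baseline adjustment, and none for follow-up scores alone.

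The practical size is unknown because c is undocumented in both size and sign. The power figures show sensitivity only. They rest on SD 9, a two-sided 5% test, design effect 2, 10% loss and, for the adjusted estimates, r = 0.5. This is a design weakness in one of the two primary outcomes. It does not invalidate the trial, and the follow-up comparison of arms remains sound. It merits correction because an unexposed baseline cannot be recovered later and the remedy is cheap.

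**What to change.** 1. **Where delivery has not begun** (Cambodia at the time of writing): complete both questionnaires, still on separate days, in every school before either cartoon is shown. Reword the two delivery sections to match. Cost: at most one extra visit to each intervention school, and MGO no longer falls on the OV baseline day.
2. **Where the same-day schedule has been used:** state which disease came first in each country. Base the second disease's primary effect on the between-arm difference in follow-up score, adjusted for the first disease's baseline (measured before any package) and country. Keep the analysis that uses the second disease's own baseline as a sensitivity analysis. Cost: some loss of precision, since the other disease's baseline is likely to predict follow-up less well.
3. **In either case where exposure occurred:** report the arm difference in the second baseline as a carry-over check, noting that it also contains chance imbalance between schools.

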#### “Magic Glasses Lower Mekong” and Acceptability Assessment

In intervention schools, delivery of the MGLM intervention package will take place on the same day as the STH KAP questionnaire, once baseline data collection is complete. The MGLM package will follow the same delivery procedures used for the MGO intervention package.

#### Follow-Up

All participants in control and intervention schools will be recruited for follow-up approximately 9 months after baseline. Participants will complete the same questionnaires for OV and STH to assess the impact of the interventions on KAP for the respective diseases. KAP scores will also provide insight on acceptability domains of intervention coherence and perceived effectiveness. In intervention schools, impact and acceptability will also be assessed using qualitative measures. FGDs will be conducted with a subset of schoolchildren in the original cohort to discuss the sustained acceptability and effectiveness of each cartoon. FGDs will also be conducted with parents of participants to investigate the indirect impact of the MGO and MGLM intervention packages on parents' knowledge of OV and STH, respectively. KIIs will be held with teachers to discuss the acceptability and impact of the cartoons on health-related attitudes and behavior.

Follow-up assessments will employ the same delivery timing as used at baseline and intervention delivery to ensure consistency and minimize confusion between OV and STH.

The trial study design is shown in Figure 2. See Multimedia Appendices for anticipated delivery times for each country.

**Figure 2 figure2:**
[figure not shown]
Trial Profile: Expected study enrollment and timeline diagram for the “Magic Glasses Opisthorchiasis” and “Magic Glasses Lower Mekong” acceptability and impact cluster randomized controlled trial. FGD: focus group discussion; KAP: knowledge, attitudes, and practices; KII: key informant interviews; MGLM: Magic Glasses Lower Mekong; MGO: Magic Glasses Opisthorchiasis.

### Data Analysis

#### Quantitative

Descriptive statistics will be computed to ascertain variable distributions.

Normality of distribution will be checked using the Shapiro-Wilk test, with significance set to *P<*.05 (2-sided). In acceptability analyses, negatively worded statements will be reverse scored to align the direction of the scale. Spearman correlation coefficient will be used to assess criterion validity among different questionnaire items. Exploratory factor analysis with oblique rotation will then be performed to assess construct validity. The primary outcome of the study is KAP scores for OV and STH.

OV and STH KAP scores will be analyzed separately. KAP scores for each questionnaire will be developed by calculating the total points for knowledge, attitude, and behavior for each student and expressed as a percentage score. Changes in self-reported KAP scores will be analyzed using linear regression. To assess the differences in KAP between control and intervention schools at baseline and follow-up, generalized-estimating equation models will be used to account for clustering within schools and repeated KAP assessment for participants. Potential confounders including age and sex will be incorporated in the model. Spearman correlation coefficient will be used to estimate correlations among acceptability, knowledge, attitudes, and self-reported behavior. Chi-square tests will also be used to measure associations between KAP and acceptability.

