The present study is designed to assess the acceptability of 2 new “Magic Glasses” cartoons, developed for the LMB, and their impact on schoolchildren’s self-reported KAP of STH and OV. Several studies have identified acceptability as a key indicator for initial and sustained intervention success [32-36]. However, there remains a lack of consistency among acceptability measures and definitions in public health research. Sekhon et al [37] developed the Theoretical Framework of Acceptability (TFA), and defined acceptability as “a multi-faceted construct that reflects the extent to which people delivering or receiving a healthcare intervention consider it to be appropriate, based on anticipated or experienced cognitive and emotional responses to the intervention” [37]. The TFA outlined 7 domains of acceptability, “affective attitude, burden, perceived effectiveness, ethicality, intervention coherence, opportunity costs, and self-efficacy” [37]. In order to conduct a robust assessment of all the domains of acceptability, the acceptability of the intervention will be assessed using mixed methods. Quantitatively using an adapted version of the TFA questionnaire [38] and qualitatively using focus group discussions (FGDs) with schoolchildren and key informant interviews (KIIs) with teachers. The KAP questionnaire will be administered at baseline and follow-up to assess the impact of the intervention, and the intervention coherence domain of acceptability.

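### Inter-item Spearman correlations are labelled as a test of criterion validity, but no criterion is named, so the trial could report a property that the analysis cannot show

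*Protocol article*

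**What the plan says.** The Quantitative part of Data Analysis lists the questionnaire checks in this order:

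- Scoring: "In acceptability analyses, negatively worded statements will be reverse scored to align the direction of the scale".
- Criterion validity: "Spearman correlation coefficient will be used to assess criterion validity among different questionnaire items".
- Construct validity: "Exploratory factor analysis with oblique rotation will then be performed to assess construct validity".

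After the KAP models, a separate analysis is given: "Spearman correlation coefficient will be used to estimate correlations among acceptability, knowledge, attitudes, and self-reported behavior". It is presented as estimating associations, not as validation.

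On the instruments themselves, the section on Magic Glasses Opisthorchiasis delivery and acceptability assessment says "The questionnaire was adapted from the TFA [38] to include age-appropriate language for the schoolchildren, and specific questions on OV". The article does not describe the adapted form as validated. Under Baseline KAP Assessment, the soil-transmitted helminth (STH) KAP form is described as already validated. For the *Opisthorchis viverrini* (OV) form, "The OV KAP questionnaire was adapted from the STH KAP and reviewed by disease experts on the project prior to finalization".

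**The concern.** The sentence fixes both a property and a method, and the two do not match. Criterion validity needs a second measurement, taken outside the questionnaire, against which the score is judged. The method stated compares items with other items, and no outside measure enters it. What it yields is a description of how far the items move together.

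This is not detail that an article leaves to a fuller document. The property and the method are both written down, and an analysis plan that followed the sentence would carry the mismatch forward.

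At stake is the wording of the validation result for a newly adapted instrument. Acceptability is the first of the stated aims, and the end of the Discussion expects the acceptability and KAP findings to inform scalability. A published statement that criterion validity had been shown would lend the questionnaire support that this analysis cannot give.

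**Working it through.** The plan gives no figure for this step, so there is none to reproduce. The check has three parts.

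**1. Is there a criterion anywhere in the article?**

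- The criterion-validity sentence names none.
- The factor analysis that follows it is also internal to the items.
- The later Spearman analysis relates acceptability to knowledge, attitudes and behaviour, but is not offered as validation.
- The Discussion describes the data as self-reported by children. No stool examination, observed behaviour or reference instrument is described as a comparator.
- Expert review of the OV KAP form bears on content, not on a criterion.

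**2. Can inter-item correlation stand in for a criterion?**

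Take the simplest model. Each of k items is √ρ·f + √(1−ρ)·e, where f is a shared factor and e is independent noise. An outside criterion has correlation γ with f. Then:

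- correlation between two items = ρ, which does not contain γ;
- correlation of the total score with the criterion = γ·√[kρ / (1 + (k−1)ρ)].

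With k = 8 and γ = 0.5, the second formula gives:

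- ρ = 0.1: 0.5 × √(0.8/1.7) = 0.34
- ρ = 0.3: 0.5 × √(2.4/3.1) = 0.44
- ρ = 0.5: 0.5 × √(4/4.5) = 0.47

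With γ = 0 it gives 0 at every ρ. Under this model, stronger inter-item correlation makes the total less noisy and so raises the criterion correlation that could be reached. It does not show whether γ differs from zero.

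**3. Simulation with five-point items**

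From the Power section: n = 114 (one arm in one country). Assumed: 8 items cut at −1.5, −0.5, 0.5 and 1.5; the values of ρ and γ; no reverse-keyed items; no school clustering; and a P<.05 flag for each of the 8 × 7 / 2 = 28 item pairs. There were 1000 replicates per setting.

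| ρ | γ | Mean inter-item Spearman | Item pairs with P<.05 | Mean Spearman, total score with criterion |
|---|---|---|---|---|
| 0.1 | 0 | 0.088 | 15.5% | 0.002 |
| 0.1 | 0.5 | 0.088 | 15.8% | 0.318 |
| 0.3 | 0 | 0.265 | 81.8% | 0.003 |
| 0.3 | 0.5 | 0.267 | 82.4% | 0.412 |
| 0.5 | 0 | 0.445 | 99.9% | 0.000 |
| 0.5 | 0.5 | 0.445 | 99.9% | 0.447 |

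Within each ρ, the planned statistic is the same, up to simulation noise, whether or not the criterion is related to the scale. The last column lies slightly below the formula values, as expected after cutting to five points and using ranks.

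In the opposite case, the items are independent and the criterion is the sum of their latent values. The mean inter-item correlation was −0.001 and the total score correlated 0.949 with the criterion. Weakly related items are a real possibility here, since the Background lists seven domains of acceptability.

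**The case against.** The strongest reply is that this is loose terminology and little more. Several parts of that reply stand.

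- **No pass rule.** A reader might infer that an invalid questionnaire would be declared valid. The article does not support that: it gives no threshold, hypothesis test or decision rule for this step, and the only significance level in that part belongs to the normality check. The most that can be said is that validity could be reported.
- **No error rate follows.** A reader might take the simulated percentages as false-positive rates for the trial. They are not. The simulation builds in correlated items and then finds them, so it illustrates a definition. Item count, loadings and the 5% flag are assumptions, and clustering is ignored.
- **Response style.** Children agreeing with everything is a tempting explanation for spurious correlation. The planned reverse scoring works against it: uniform agreement would lower correlations between oppositely worded items. A general tendency to answer favourably could still raise them, but the article gives no evidence on that.
- **Other evidence on acceptability.** A reader might suppose that the first aim rests on this questionnaire alone among quantitative instruments. It does not. The Background says "In order to conduct a robust assessment of all the domains of acceptability, the acceptability of the intervention will be assessed using mixed methods", and both the Background and Follow-Up sections assign KAP scores a role in acceptability domains. Sustained acceptability rests on focus groups and interviews. Nor does the article say that its scale-up argument depends on a criterion-validity result.
- **Ambiguity.** The sentence does not say which questionnaire is meant, and the appendices with the instruments are not shown. It might mean items across questionnaires. That would be closer to convergent evidence, but it would compare self-reports from the same children and still name no criterion.

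What does not stand is the suggestion that the later Spearman analysis already fills the gap. It is not presented as validation, and no expected relation is stated for it.

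**Conclusion.** The concern holds as a minor point. As written, the plan attaches the name criterion validity to an analysis that describes association among items, and it names no outside criterion. The trial could therefore report a property that the analysis cannot show.

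The conclusion rests on the definition of criterion validity and on reading the sentence as concerning the acceptability questionnaire, which its position makes most likely. On the across-questionnaire reading, the sentence would still need to state its criterion. The conclusion does not rest on the simulation settings.

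The reach is limited. The primary comparison of KAP scores by generalized estimating equations is unaffected, and this step is not said to remove items or change any score.

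**What to change.** Replace the sentence with: *Inter-item Spearman correlations will be used to describe internal consistency of the acceptability questionnaire; no claim of criterion validity will be made from them.* This also settles which instrument is meant.

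If a criterion-validity claim is wanted, name before the analysis a measure outside the questionnaire that the trial already collects, state the correlation expected, and correlate the total acceptability score with it. The measure must already exist because the Results section reports the trial as in progress in two of the three countries. KAP scores are the other quantitative measure that the article describes for the same children. They would be a weak criterion, being self-reported and already used to inform acceptability domains. Entries to the drawing and essay competitions should not be assumed available, since the article does not say that they are recorded per child.

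The cost of the first option is one sentence and the loss of the criterion-validity claim. The second keeps the possibility of a claim, but only as strong as the measure chosen. Neither needs new participants or touches the primary analysis.

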### Consent and Recruitment

Based on local expertise on school student numbers in each country, approximately 6 schools will be selected in each country to achieve a total sample size of 228 per country. Prospective schools will be selected in consultation with the local departments of education. Once schools are identified, permission to conduct the study will be sought from the principal of each selected school. Teachers and parents or legal guardians of prospective participants will then receive an information sheet outlining the procedure and purpose of the study and contact information, and a consent form. On receiving the written parental or guardian consent, the aims, process, and outcome of study will be explained to prospective student participants and their written assent will be sought. Only schoolchildren who have provided informed assent and parental consent will be included in the study. Teachers and parents will be recruited a month before follow-up. As part of the recruitment process, an information sheet will be provided and informed consent will be sought. Once written consent is obtained, teachers and parents will be recruited into the study.

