### Power

The sample size was calculated to achieve 80% power, assuming baseline knowledge of 30 percentage points (as reported in the original “Magic Glasses” intervention by Bieri et al [31]) and a design effect of 2 to account for cluster sampling. Accounting for 10% attrition, it was estimated that a total of 227 participants would be needed to detect a difference of 5 percentage points in knowledge between intervention and control groups. As such, we will aim to enroll a total of 228 schoolchildren in years 3-5 (114 in intervention arm, 114 in control arm) in each country.

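### Two analyses are named for the primary KAP outcome, neither is designated primary, and only one of them is said to account for school

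*Protocol article*

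**What the plan says.** The Protocol article, under Data Analysis (Quantitative), states that "The primary outcome of the study is KAP scores for OV and STH", with the two diseases analysed separately. It then gives two methods in consecutive sentences. The first is "Changes in self-reported KAP scores will be analyzed using linear regression". The second concerns the contrast between control and intervention schools at the two time points, for which "generalized-estimating equation models will be used to account for clustering within schools and repeated KAP assessment for participants"; age and sex enter as covariates. Clustering is mentioned only in the second sentence, and neither method is called primary.

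Under Randomization, "Schools within each country will be randomly allocated to control or intervention arm". Under Consent and Recruitment, "approximately 6 schools will be selected in each country to achieve a total sample size of 228 per country". Under Power, the sample size uses "a design effect of 2 to account for cluster sampling".

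**The concern.** In a trial randomised by school, a comparison of arms that treats pupils as independent gives standard errors that are too small. The plan recognises this when it sizes the trial and again when it specifies GEE, but not in the sentence on change. Change from baseline to 9 months is a natural way to express impact in a cohort measured twice, so the regression could readily be read as a test of the intervention. A repeated-measures GEE can already estimate change by arm. The regression is therefore either redundant or a competing test that makes no stated allowance for school. With no order of precedence, two P values could exist for the primary outcome, one of them falsely precise, and the choice between them could be made after the results are seen.

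**Working it through.** **Inputs from the article.** Design effect (DE) 2 (Power). About 6 schools and 228 pupils per country (Consent and Recruitment), so 228/6 = 38 pupils per school and about 18 schools in three countries. Two-sided 5% significance is stated only for the normality check; I assume it for the KAP comparison.

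**The plan's own figure.** The 227 per country cannot be reproduced, because no standard deviation is given. Working back: 227 × 0.9 = 204.3 after attrition; divided by 2 arms and by DE 2, that is 51.1 effective pupils per arm. The implied SD is 5 × √(51.1/2) / (1.960 + 0.842) = 9.0 points (two-sided). Nothing below depends on it.

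**Implied intraclass correlation.** DE = 1 + (m − 1) × ICC, so 2 = 1 + 37 × ICC and ICC = 1/37 = 0.027.

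**True size of a between-arm test with naive standard errors.** If the variance is understated by the factor DE, the true two-sided size is 2 × [1 − Φ(1.96/√DE)], and the interval has 1/√DE of its proper width.

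| DE | 1.96/√DE | True size | Ratio to 5% |
|---|---|---|---|
| 1.25 | 1.753 | 0.080 | 1.6 |
| 1.5 | 1.600 | 0.110 | 2.2 |
| 2 | 1.386 | 0.166 | 3.3 |
| 2.5 | 1.240 | 0.215 | 4.3 |
| 3 | 1.132 | 0.258 | 5.2 |

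At DE 2 the 95% interval is 1 − 1/√2 = 29% too narrow.

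**Simulation check** (20,000 null trials, 38 pupils per school, ICC 1/37), proportion rejected at nominal 5%:

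| Method | 6 schools | 18 schools |
|---|---|---|
| Linear regression, naive errors | 0.166 | 0.165 |
| GEE, uncorrected sandwich variance, normal reference | 0.186 | 0.083 |
| t test on school means | 0.050 | 0.049 |

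The first row agrees with the formula. The second shows that naming GEE does not by itself secure the error rate with so few schools. The third shows that a method suited to the number of schools does.

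**The case against.** The strongest reply is that the plan does not ignore randomisation by school. A reader who stops at the regression sentence might infer that the primary comparison is made by ordinary least squares and that its false-positive rate is roughly tripled. The documents do not support that. The next sentence gives the comparison of arms to GEE with school clustering. The article does not call the regression ordinary, does not exclude cluster-robust errors, and does not say that it tests arm: it could describe change within arms, or be loose wording for the same model. The primary outcome is KAP scores, not explicitly change. The design effect of 2 belongs to the sample size for knowledge, and none is given for change. All of this stands and limits the finding.

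A reader might also infer that the correlations, and the plan that "Chi-square tests will also be used to measure associations between KAP and acceptability", suffer the same inflation. They do not. Both variables there are measured on pupils, so the design effect is roughly 1 + (m − 1) × ICC₁ × ICC₂. With both ICCs at 0.027 that is 1 + 37 × 0.027² = 1.03. In simulation with 9 intervention schools (6,000 runs) the size was 5.1% for Spearman and 5.0% for chi-square. With both ICCs at an assumed 0.10 it was 8.8% and 6.8%. Nor does the text show that chi-square means cutting up the percentage score, since the acceptability questionnaire includes multiple-choice items.

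Finally, precedence between models and small-sample corrections are often left to an analysis plan, and none is shown. That is fair for the GEE correction. It does not dispose of the main point, because the regression of change is a method the article itself states for the primary outcome family. Even a within-arm estimate of change would have too small a naive standard error if change is correlated within school.

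**Conclusion.** The concern holds in a limited form. Two overlapping analyses are stated for the primary outcome, the allowance for school is attached to only one, and neither has precedence. The harm is conditional: it arises if the regression of change is used to compare arms with naive standard errors. In that case a nominal 5% test has a true size of about 17% at a design effect of 2. Because the value for change is unknown, the defensible statement is a range, about 8% to 26% for assumed design effects of 1.25 to 3. The finding does not extend to the GEE comparison as such, or to the acceptability associations.

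**What to change.** Name one primary analysis for each disease: 9-month KAP score by arm, accounting for school through a mixed model or a GEE clustered on school, adjusted for baseline score and for country, within which schools are randomised. State a small-sample correction, given about 18 schools overall and about 6 in any single-country analysis (where the country term drops out). For the linear regression of change, do one of three things: drop it, state that it too accounts for school, or label it descriptive only.

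This changes analysis wording and needs no new data, since baseline score and country are already recorded. The price is wider intervals: at a design effect of 2, by a factor of √2 = 1.41 relative to the naive regression, and somewhat more once the small number of schools is allowed for. The wording should be settled before outcome data are analysed.
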